## Abstract

**Background:**

Suicide is a national public health crisis and a critical patient safety issue. It is the 10th leading cause of death overall and the second leading cause of death among adolescents and young adults (15–34 years old). Research shows 80% of youth who died by suicide saw their primary care provider within the year of their death. It is imperative that primary care providers develop the knowledge and skills to talk with patients about distress and suicidal thoughts, and to assess and respond in the context of the ongoing patient - primary care provider relationship.

**Methods:**

This study examines the effectiveness of simulation on suicide prevention training for providers-in-training by comparing two conditions: 1) a control group that receives online teaching on suicide prevention in primary care via brief online videos and 2) an experimental group that includes the same online teaching videos plus two standardized patient (SP) interactions (face-to-face and telehealth, presentation randomized). All SP interactions are video-recorded. The primary analysis is a comparison of the two groups’ suicide prevention skills using an SP “test case” at 6-month follow-up.

**Discussion:**

The primary research question examines the impact of practice (through SP simulation) over and above online teaching alone on suicide prevention skills demonstrated at follow-up. We will assess moderators of outcomes, differences among SP simulations (i.e., face-to-face vs. telehealth modalities), and whether the experimental group’s suicide prevention skills improve over the three SP experiences.

**Trial registration:**

The study was registered on Clinical Trials Registry (clinicaltrials.gov) on December 14, 2016. The Trial Registration Number is NCT02996344.

## Background

Suicide is a national public health crisis and a critical patient safety issue. Suicide is the 10th leading cause of death overall and the second leading cause of death in adolescents and young adults (15–34 years old) [1]. For every death by suicide there are approximately 25 suicide attempts that do not result in death [2]. Individuals who survive suicide attempts ultimately experience much higher rates of mental and physical health issues compared to non-attempters [3]. Despite a variety of national prevention efforts including the Surgeon General’s National Strategy for Suicide Prevention, suicide rates, including among youth and young adults, have climbed over the past two decades [4].

A recent U.S. study of suicide reported that 45% of individuals who died by suicide had contact with primary care services within one month before their death [5]. Another study found that 80% of youth who died by suicide saw their primary care provider within a year of their death [6]. Suicidal patients are more likely to see a primary care provider than a mental health professional. In fact, only 20% of individuals who died by suicide saw a mental health provider within a month of their death, compared to 45% of suicidal individuals who saw a primary care provider within a month of their death [5, 7].

Training health care providers is likely to reduce suicide attempts and deaths [8], and suicide is deemed a “Never Event” by the National Quality Forum. Yet training in suicide prevention is not required in most medical and post-graduate education programs [9] and only a few states require it for licensure. Where training does exist, its effectiveness has not been studied and there is no consensus on the best methods for improving the care of suicidal patients.

One promising methodology for training providers in suicide assessment and safety planning skills is simulation. There is a long history of simulation-based learning methods in medical [10] and nursing school [11] training programs. Since 1963, standardized patients (SPs; specially-trained actors who present patient scenarios, symptoms or signs and feedback) have been used as an active learning education tool for teaching and learning. Systematic reviews have shown evidence for improvements in learners’ knowledge and confidence with high fidelity simulation methods [12, 13] including resident screening for adolescent depression [14]. Feedback from simulated patient interactions has been used successfully in psychiatry resident education to teach suicide assessment skills [15]; however, these methods have not been applied to other health professionals such as primary care providers, and the effect of standardized patient practice has not been directly measured in a controlled study.

Another challenge for medical education programs is to prepare trainees for technological advances in health care, including rapidly increasing use of telemedicine contact with patients via telephones, smartphones, and mobile wireless devices, with or without a video connection [16, 17]. Patients living in rural communities and those with mental health needs are particularly likely users for telehealth care [18, 19]. There are currently barriers to routine telehealth practice (e.g., reimbursement, access); however, given the trends in healthcare, studies on ‘remote’ provider-patient interactions are critical. To our knowledge, there are no studies of telehealth-based suicide risk assessment and management.

The current study responds to the need for effective suicide prevention training for primary care providers [11]. The primary research question asks whether experiential and reflective practice, via standardized patient simulation and feedback, improve suicide prevention skills over and above expert teaching alone. We test simulation as a component of the training because, while resource-intensive, it involves techniques that are core tenets of adult learning and is highly likely to be effective [20]. We incorporate specific feedback into the training as it has been shown to be a key component of learning new skills in the medical field [21]. Assurance of providers’ ability to identify and effectively respond to those who are suicidal is an ideal use of simulation-based training and assessment methods [22]. We include telehealth as a modality in the experimental condition with the knowledge that it will soon be a normative practice for primary care providers and to contribute to our understanding of interventions with suicidal patients.

This randomized control trial (RCT) examines the effectiveness of simulation and feedback, using standardized patient (SP) interactions, on the suicide risk assessment and management skills of primary care providers-in-training. There are two groups: 1) a control group that receives online teaching delivered via brief videos and, 2) an experimental group that receives the same brief videos followed by two SP practice experiences with feedback – one face-to-face and one telehealth. Both groups’ skills are tested via an in-person SP “test case” at 6-month follow up. All SP interactions are followed by immediate feedback given by the SP that is specifically linked to training concepts.

Hypotheses are as follows: 1) All participants will gain suicide prevention knowledge from baseline after viewing online teaching and will maintain improvement at 6-month follow-up; 2) Participants in the experimental group will report greater satisfaction with the training, greater self-efficacy in identifying and responding to patients with suicidal thoughts and plans, and greater intention to use, as well as reported use of suicide prevention skills at 6-month follow-up; and 3) Participants in the experimental group will also be more skillful in responding to suicidal patients (demonstrated during the SP “test case” interview as measured by objective, observed ratings) compared to the control group at 6-month follow-up. Additionally, we will examine moderators of outcomes, differences between the two SP simulation modalities (i.e., face-to- face vs. telehealth modalities), and if there is improvement in skills observed over multiple SP interactions for the experimental group.

## Methods

### Aim

This study aims to compare online teaching alone to online teaching plus practice through simulation on the suicide risk assessment and safety planning skills of primary care providers-in-training.

### Design

The study is a randomized controlled trial with an experimental group and a control group allocated with a 1:1 randomization ratio. All trainees are randomized to control and experimental learning groups using Wei’s urn randomization [23] which provides overall balance at the end of accrual but also gives good, often near-perfect, balance within many strata [24, 25]. Randomization strata include medical learner groups (i.e., medical residents, pediatric residents, and nurse practitioners) and gender. After all baseline measures are completed, participants are randomized to experimental condition by the project statistician, who remains blinded to study condition.

Participants in both groups complete a 48-min, 6-module, online video-based training on suicide prevention (Commitment to Living for Primary Care; CTL-PC). Upon completion of the online teaching program, participants in the experimental group engage in two standardized patient practice interactions over the course of 4 to 6 months. One practice interaction takes place in-person and the other uses a telehealth model. The order is randomized. Then, approximately 6 to 8 months (depending on schedules, see below) after video-based learning, both control and experimental groups engage in an in-person “test case” standardized patient interaction.

### Setting

The suicide prevention training occurs in the context of pediatric and family medicine residency and nurse practitioner training programs at the University of Rochester Medical Center. SP sessions are conducted at the convenience of the participants at several medical training sites including the University of Rochester School of Nursing, Strong Memorial Hospital, the Department of Family Medicine, and the Rochester General Pediatric Associates. Each SP interaction takes place in a private room and the entire session is a maximum of one hour in duration. In the case of telehealth interactions, standardized patients are in a different location from participants.

### Participants

Participants are second year trainees from two education programs at the University of Rochester Medical Center: the nurse practitioner training program (NP) and medical residency programs, which included second year residents from pediatrics, the combined internal medicine-pediatrics program, and family medicine. These learner groups were chosen because most are preparing for careers in primary care. The training directors of the programs agreed to incorporate suicide prevention training into their curriculum for the duration of the grant and to support randomization of learners. As a result, all trainees receive the training according to their randomized condition. Trainees engage in a consent process (conducted by study personnel) for analysis of their data; those who do not consent for the study receive the training but their data are not analyzed. All trainee participants are fully informed that the SP interactions are part of their suicide prevention training. We collect non-identifiable demographic data at baseline for all trainees in order to compare those who enrolled in the study and those who did not. We plan to enroll 108 participants generally divided between residents and NPs.

### Online teaching

“Commitment to Living for Primary Care” (CTL-PC) was adapted for primary care from an evidence-based suicide prevention training program for mental health professionals that has been widely disseminated [26, 27]. The online teaching was presented by one of us (AP) who has had more than a decade’s experience training clinical staff in the evaluation of suicidal persons. CTL-PC consists of six brief video modules (48 min in total) that focus on practical aspects of person-centered care for patients with suicidal thoughts and plans. The modules are as follows: introduction to suicide prevention in primary care; person-centered approach to asking about suicide in primary care; gathering data to inform risk assessment; synthesizing data into a formulation of risk; responding to acute and ongoing risk in primary care; and special considerations (adolescents, substance abuse, intimate partner violence, and LGBT).

### Procedures

Following enrollment, participants receive an email with instruction to complete online baseline assessments and view the teaching videos within 14 days. All surveys are completed online using the same secure website that hosts the CTL-PC videos. After they have viewed the videos, participants in the experimental condition engage in two practice SP interactions over a period of about four months, with at least one month between interactions. Participants in the control condition do not have practice interactions. At approximately six months following completion of online teaching, both experimental and control participants complete the same face-to-face SP test case. There are two SP character scenarios for the experimental practice sessions and one test case SP scenario.

As part of their practice experience, experimental participants engage in telehealth and face-to-face SP interactions; the order of presentation is randomized. The SP practice character scenario is also randomized (male/female) for the experimental group. All interactions are video-taped for observational coding of suicide prevention skills. In the telehealth modality, the participant and standardized patient are in different locations and interact using a secure webcam service. The face-to-face modality occurs in an office setting. The procedures for face-to-face and telehealth interactions are the same and no more than one hour in duration, including: orientation to the procedures and the SP scenario backstory, up to 30 min for the SP interaction, 8 min for SP feedback for the participant, and 5 to 10 min for debrief procedures. Upon arrival to the interaction, participants are introduced to the procedures and are given a brief written backstory about the SP scenario. Backstories provide context for the provider and include details about the patient’s name, age, the nature of the patient-provider relationship, some medical and social history and the reason for this visit (“trouble sleeping”). Telehealth participants also receive instructions about remote access. Participants are instructed to assess the patient’s risk for suicidality and provide appropriate interventions within a 30-min timeframe (a timer signals the appointment end). After the interaction, participants exit the room for 10 min during which time the SP prepares immediate feedback (positive and constructive) for the patient. SPs are highly trained to prepare and deliver tailored feedback using a 15-item “feedback matrix” template of criteria for identifying appropriate feedback items. Feedback includes specific competency items with explanations and rationale for the importance of the skill. The participant joins the SP for 8 min to receive feedback, discuss the interaction and ask questions. Afterwards, the participant returns to the facilitator for 5 to 10 min of debrief procedures. During this time, participants are provided the opportunity to speak with a psychologist for further debriefing if needed.

All interactions are recorded, securely stored and subsequently coded for observed suicide prevention skills. A portion (at least 20%) of recorded interactions are double coded for inter-rater reliability. Consensus meetings are conducted and discrepancies are resolved through discussion. Additionally, the videos are coded for SPs fidelity to the scenario and feedback procedures. To avoid drift in standardized procedures, SPs receive written feedback on fidelity to the character and feedback delivery.

After the SP test case at approximately 6-month follow-up, all participants complete a final survey including: knowledge and self-efficacy measures, retrospective self-report of transfer of training, intentions to use the suicide prevention training in future practice, self-reported use of suicide prevention skills since the online teaching program, and satisfaction with various aspects of the training.

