##### Feedback matrix

Immediately following each interaction, SPs prepare feedback for the participant on 15 items and document the ratings on a Scantron-style form. SPs verbally provide participants with six feedback items – three positive and three constructive. Several items are prioritized as feedback items to provide to the participant. In the case of experimental participants’ second and final sessions, SPs have information on the feedback items that have been previously provided to the participant as guidance for novel feedback.

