#### Hypotheses and exploratory analyses

##### Hypothesis 1

All participants will demonstrate improved suicide prevention knowledge from baseline after viewing the online teaching videos. We anticipate that this improvement will be maintained at the 6-month SP assessment. We do not anticipate a difference between the two conditions on knowledge measures. Repeated measures analysis of variance will be used to examine change in knowledge scores. Time will be examined as a within-subject factor (pre, post-videos, and follow up) with group entered as a between-subjects factor. Specifically, we hypothesize an overall time effect but no group or group by time interaction effects. Tryon’s inferential confidence intervals (ICI) will be used to assess for equivalency across treatment groups immediately post videos and immediately after the SP test case [31, 32]. In general, these inferential confidence intervals are adjusted so that “statistical difference” equates to two inferential confidence intervals that do not overlap (i.e., abutting at the upper or lower bounds). Establishing traditional 95% confidence intervals about each of two means, and concluding that the means differ *p* < .05 if the two intervals do not overlap, constitutes a greater burden of proof of statistical difference than would a corresponding t-test. To establish equivalence, however, a “Minimum Important Difference” (MID) must be established a-priori. By establishing MID’s, a context for determining statistical difference, equivalence, and indeterminacy is provided. Statistical differences exist when ICI’s do not overlap; statistical equivalence exists when the maximum probable mean difference estimate provided by the ICI (maximum upper bound of mean 1 and 2 minus the minimum lower bound of mean 1 and 2) is less than the MID and statistical difference does not exist. Indeterminacy exists when the means are neither statistically difference nor significantly equivalent. Following Treadwell and colleagues [33] a standardized small effect of .20 [34] will define the criterion for establishing a MID. As a form of sensitivity, a MID of .10 will also be examined.

##### Hypothesis 2

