Participants in the experiment condition (simulation and feedback) will report greater self-efficacy in identifying and responding to patients at risk for suicide and greater intention to use the skills at 6 months compared to the control condition (those who only complete online teaching). We will use ANCOVA to assess SP training effects on satisfaction with the program, self-efficacy in identifying and managing patients who are at risk for suicide, and greater intention to use the skills at follow up. In all instances, the stratification variables of gender and training program group, as well as race/ethnicity/age and baseline status of the dependent variable (i.e., self-efficacy), will be included as covariates to aid in statistical power [35, 36]. If ceiling effects become an issue in any of these outcomes, tobit regression [37] will be used with the same covariates to assess for condition differences.

##### Exploratory analyses for Hypothesis 2

Moderation effects will be explored. The same ANCOVAs/tobit regressions described above will be conducted for each analysis but will also include interaction effects. Specifically, the cross-product of experimental condition by training group, baseline previous experience with suicidal patients, previous suicide prevention training, and baseline knowledge will be separately entered into each of the analyses. Procedures outlined by Aiken & West [38] will be used to minimize problems associated with multicollinearity. Multiplicative terms will be computed, first by centering each predictor variable and then forming the product term using the centered predictors of interest. Effect sizes, following Lipsey & Wilson [39], will also be examined as power to detect significant interactions will be limited [40]. The goals of these exploratory moderator questions are to better understand for whom the simulation training might be more effective (e.g., Do simulation training effects differ based on previous trainings/experiences with suicidal patients? Do simulation effects differ by training program group?).

##### Hypothesis 3

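### The follow-up knowledge, self-efficacy and intention items come after the SP test case and its feedback, so they compare three SP sessions with one rather than practice with online teaching alone

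*Protocol article*

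**What the plan says.** Procedures states that at about six months "both experimental and control participants complete the same face-to-face SP test case". It then places the self-report: "After the SP test case at approximately 6-month follow-up, all participants complete a final survey including: knowledge and self-efficacy measures". The same survey holds the transfer, intention, use and satisfaction items.

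The test case carries feedback. Background says: "All SP interactions are followed by immediate feedback given by the SP that is specifically linked to training concepts". The Feedback matrix section agrees: "Immediately following each interaction, SPs prepare feedback for the participant on 15 items". It also covers the last visit explicitly: "In the case of experimental participants’ second and final sessions, SPs have information on the feedback items" already given to that participant. Procedures describes the content as instructional: "Feedback includes specific competency items with explanations and rationale for the importance of the skill".

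Under Hypothesis 1, knowledge is to be tested for "equivalency across treatment groups immediately post videos and immediately after the SP test case", and the gain is expected to persist to the 6-month SP assessment. Under Hypothesis 2, the experimental arm is expected to report "greater self-efficacy in identifying and responding to patients at risk for suicide and greater intention to use the skills at 6 months", against a control condition defined as online teaching and nothing more.

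**The concern.** SP interaction plus tailored feedback is the active component of the experimental arm. Controls receive one dose of it immediately before they rate self-efficacy and intention. The definition of controls in Hypothesis 2 is then no longer true at the moment of measurement, and the comparison is not the one stated under Aim.

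For Hypothesis 1, both arms take the follow-up knowledge test just after practice and coaching linked to the training content. A score that has held up could reflect retention over six months, the recent refresher, or both. The between-arm equivalence test at that point has the same difficulty, because both arms share a recent exposure.

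**Working it through.** **Sequence up to the follow-up survey**

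| Step | Control | Experimental |
|---|---|---|
| Baseline survey, videos, post-video survey | yes | yes |
| Practice SP sessions with feedback | 0 | 2 |
| Test-case interaction (source of the coded skills) | 1 | 1 |
| Test-case feedback | yes | yes |
| Final survey | yes | yes |
| SP sessions with feedback before the final survey | 1 | 3 |

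No single sentence gives the order of feedback and survey within the test-case visit. It is inferred: feedback is immediate, and the survey follows the test case. No follow-up survey before the test case or before its feedback is described.

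**Outcomes affected**

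- Affected: follow-up self-efficacy, transfer/intention and knowledge.
- Not affected: Hypothesis 3, because the skills are coded from the test-case interaction, which precedes its feedback. The knowledge change across the videos and the post-video equivalence test are also safe, because they precede any SP session.
- Little affected: self-reported use, which looks back over the time since the online teaching.
- Rightly placed: satisfaction with the SP experience, which controls can report only after the test case.

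**Size, as an illustration only**

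Let G(k) be the gain on an outcome after k sessions. The intended contrast is G(2) − G(0); the measured one is G(3) − G(1). The loss is

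[G(2) − G(0)] − [G(3) − G(1)] = [G(1) − G(0)] − [G(3) − G(2)].

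The contrast shrinks only if the third session adds less than the first.

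- Equal gains per session: 2 − 0 = 3 − 1, so there is no loss.
- Each session closes half the remaining gap (assumed), G(k) = 1 − .5^k: G(0) = 0, G(1) = .5, G(2) = .75, G(3) = .875. Intended contrast .75; measured .875 − .5 = .375, a 50% loss.
- A first encounter that lowers confidence, G(1) < G(0), with a third session that does no harm: the loss is negative and the contrast widens.

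**Power in the halving case**

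Inputs: N = 108 and effect size .30 (Power analyses), 1:1 allocation (Design), α = .05 (Data processing; two-sided assumed). Normal approximation: power ≈ Φ(d/√(1 − R²) × √(N/4) − 1.96).

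- Check on the plan's own figure, d = .30, R² = .40: .30/√.60 × √27 = 2.01; power .52 (.51 with the t distribution). The plan states .51, so the method reproduces it.
- d = .30, R² = .50: .30/√.50 × √27 = 2.20; power .60.
- d = .15, R² = .50: 1.10; power .20.

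The plan states .80 for the middle case, which this formula does not reproduce. That is a separate matter; the starting point here is the recomputed .60.

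**The case against.** The strongest reply is that both arms take the same test case, so the randomised comparison stays valid and only its meaning shifts, to three sessions against one. That stands. A reader might infer that Hypotheses 1 and 2 are invalid throughout, or that the trial's main result is compromised. The document supports neither: the primary outcome and the post-video knowledge results are untouched, and satisfaction and use need not move.

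A reader might also take the 50% dilution as an estimate. It is not one. The halving curve has no source in the document, equal gains give no dilution, and the plan does not say that its .30 refers to two sessions against none. Any dilution would make a positive Hypothesis 2 result conservative, but the direction is not established either.

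On knowledge, the feedback is six verbal items in 8 minutes, tailored to observed behaviour, whereas the test has 17 multiple-choice items. Their overlap is not documented, so the refresher may be weak. It is nevertheless linked to the training content and cannot be separated from retention.

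Finally, the present order protects the primary outcome. Self-efficacy items on asking directly about suicide and on safety planning, given before the test case, could prime the skills being coded. This stands, and it rules out moving the survey ahead of the test case.

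**Conclusion.** The point holds as a secondary design limitation. As scheduled, follow-up Hypothesis 2 on self-efficacy and intention compares three SP-with-feedback sessions with one, and the description of controls as having had online teaching only is wrong at that time. Follow-up knowledge in Hypothesis 1, both its maintenance and its between-arm equivalence, cannot be separated from a shared recent refresher.

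Confidence is high on the sequence, given the inferred order of feedback before survey. It does not extend to the size or direction of the effect. Dilution is zero with equal gains and 50% under the assumed halving curve, and the contrast could widen if a first encounter lowers controls' confidence.

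**What to change.** For remaining participants, collect the self-efficacy and transfer/intention items, and the knowledge items if time allows, in the 10-minute break while the SP prepares feedback. Do not place them before the test case. Leave satisfaction and use at the end. Amend the survey timing in Procedures and the equivalence time point under Hypothesis 1 to match, and record when each survey was taken, so that participants already surveyed after feedback can be distinguished.

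The costs are real:

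- **Time.** Self-efficacy and transfer come to 20 + 8 = 28 items, and knowledge brings this to 45, before the intention items.
- **Residual exposure.** The SP interaction itself still precedes the items; only the feedback is removed.
- **Mixed timing.** The trial is under way, so two measurement times would be mixed within an outcome.

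If these costs are judged too high, keep the order and change the wording. State follow-up Hypothesis 2 as three against one SP-with-feedback sessions. State that follow-up knowledge is measured after a refresher, and do not claim it as unassisted maintenance. This costs only text.
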